#### Data processing and selection

Marker and force plate data will be processed using the MOX files in custom made MATLAB software (MATLAB 9.0, R2016a, The Mathworks Inc., Natick, MA, USA). Marker tracks will be filtered with a low pass second order, zero-phase Butterworth filter, with a cut-off frequency of 12 Hz and force data will be filtered with a frequency of 20 Hz. Events (initial contact and toe off) will be calculated using combined force plate data (50 N threshold) and foot marker data (change of velocity direction) [45]. Combining these two methods will improve the accuracy of gait events detection in the center of the treadmill, triggering both force plates simultaneously. For all steps the foot marker data will be used and this timing will be corrected based on the average discrepancy between the force plate data and the foot marker data for the correct steps (triggering only one force plate). Correct kinetic steps will be selected automatically by the MATLAB software. A visual check will be performed and eventual wrong detected kinetic steps will be corrected. For EMG processing, gait events will be determined based on marker data, since force plate data is not included in the file with raw EMG signals (C3d extension). Next, all data are time-normalized into gait cycles (0–100%) based on two successive heel strikes. For each condition per participant, the approximately 125 recorded gait cycles are subsequently averaged to ensemble one average curve.

#### Spatiotemporal parameters

The following spatiotemporal parameters will be computed: walking speed (m/s), cadence (steps/min), stride time (time from initial contact to the next ipsilateral initial contact), stride length (distance between the toe marker at the second metatarsal head (MT2) and the ipsilateral MT2 marker at each initial contact in the anteroposterior direction, corrected for treadmill speed), step width (distance between the MT2 markers in mediolateral direction between both feet at initial contact) and double support time (s). Step time (s, time from one initial contact to the contralateral initial contact), stance time (s, time between initial contact and toe off of the ipsilateral leg), swing time (s, time between toe off and initial contact of the ipsilateral leg) and step length (m, distance between the toe markers in anteroposterior direction between both feet at initial contact) will be computed for right and left separately.

Minimal foot clearance (MFC) calculation is based on the second metatarsal head (MT2) marker, placed on the shoe. The height of this marker during stance phase is subtracted from the height during swing phase. This smallest relative height of MT2 during swing phase reflects the MFC. The relevant questions on this level is: *Does FES improve toe clearance?* The other spatiotemporal parameters will be used as descriptions of the gait pattern.

#### Kinematic data

Using the HBM II lower limb with trunk kinematic model with functional hip and knee calibration, kinematics in the sagittal and transversal plane of the ankle, knee, hip and trunk will be calculated based on inverse dynamics. The relevant questions on this level are: *1) Does FES improve ankle dorsiflexion in swing phase, especially in mid-swing and at initial contact? 2) Does FES improve the ankle range of motion during walking, from maximal plantarflexion pre-swing to maximal dorsiflexion during swing? 3) Does FES change ankle kinematics in the transversal plane (foot progression angle)?* Data of hip and knee will be used for general description of gait pattens and will be taken in to account for describing changes in MFC.

#### Kinetics

Force plate data and kinematic data will be synchronized. For the ankle, the moment (dorsiflexion/plantarflexion) and power (generation/absorption) will be calculated over the gait cycle. The relevant question on this level is: *Does FES change ankle plantarflexion force at push-off during gait, compared to AFO or no walking aid?*

#### Stability

Gait stability is a complex task and several measurements exist, of which the margin of stability (MoS) is one, measuring the minimum distance from the velocity-extrapolated center of mass to the boundaries of the base of support.(46)The MoS is calculated as the difference between the boundary of the base of support (BoS), based on the lateral malleoli markers, and the extrapolated center of mass [46]. The anteroposterior MoS is calculated at initial contact and the treadmill belt velocity is taken into account. For the mediolateral MoS the smallest value during a step is used. The relevant questions on this level is: *Does FES change stability during walking?*

#### EMG

The raw data (C3d file) from the gait analyses will be exported and loaded into MATLAB. The raw sEMG signals are band-pass filtered at 10 to 500 Hz using a 4th order Butterworth filter to remove low frequency motion artefacts and high frequency noise [47]. Subsequently, a linear envelope of the data is produced using full wave rectification and root mean square average with a 100 ms time window. The sEMG amplitudes are, within each gait cycle, normalized to the peak amplitude of the muscle. For each participant, the approximately 125 recorded gait cycles are subsequently averaged to ensemble one average curve of muscle activity. The onset and duration of the muscle activity are determined based on this curve. A muscle is considered to be active if the amplitude value exceeded 20% of the peak activation [47]. This protocol will be applied for each muscle. To compare several measurements, the burst duration similarity index (BDSI) will be determined [48]. This index indicates the percentage that the muscle activation patterns in two of the measurements match during the gait cycle.

In another analysis, median frequency and amplitude of the EMG per gait cycle during and after the fatigue protocol will be analysed to explore signs of fatigue.

The relevant question on this level is: *Does FES decrease muscle activation of the calf muscles?*

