**Fig. 2 Fig2:**
[figure not shown]
The WalkAide device positioned on the leg. The orange indicator at the top is visible. Image:© 2020 Innovative Neurotronics, Inc., All rights Reserved. Usage in paper allowed

Surface electromyography (sEMG) is used to evaluate the timing of the stimulation during the gait cycle. This is more precise than relying on the ‘auditive feedback’ from the WalkAide device that can be turned on to hear the timing of the stimulation during walking. With a quick set-up of three markers on the foot (caput of metatarsal bone 2 and 5 and the heel) and one sEMG sensor on the tibialis anterior muscle, the on/off timing of the stimulation during the gait cycle can be visualized in a 3D gait laboratory. This set-up is not used for gait analysis but only for evaluation of the timing of the stimulation. Figure 3 shows the FES stimulation in the EMG as big spikes. The goal is to let the stimulation start just after toe-off and let it stop just after heel strike. In the WalkAnalyst software, it is possible to adjust the thresholds for on/off and the durations of stimulation and no stimulation.4.Stimulus intensity

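### Scaling each gait cycle to its own peak lets the EMG outcomes show timing and pattern, but not a uniform fall in the level of calf activation

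*Protocol article*

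**What the plan says.** All the rules stand in the EMG section of the protocol article.

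- Scaling: "The sEMG amplitudes are, within each gait cycle, normalized to the peak amplitude of the muscle". About 125 scaled cycles are then averaged into one curve.
- Outputs: "The onset and duration of the muscle activity are determined based on this curve".
- On/off rule: "A muscle is considered to be active if the amplitude value exceeded 20% of the peak activation".
- Comparison between measurements: the burst duration similarity index (BDSI), of which the section says "This index indicates the percentage that the muscle activation patterns in two of the measurements match during the gait cycle".
- Question to be answered: "Does FES decrease muscle activation of the calf muscles".

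The only EMG amplitude analysis described is a separate one, in which "median frequency and amplitude of the EMG per gait cycle during and after the fatigue protocol will be analysed to explore signs of fatigue".

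The Equipment section lists gastrocnemius medialis and soleus among the recorded muscles. The gait analysis Procedure section lists five conditions, including comfortable speed with the aid (condition 1) and comfortable speed without it (condition 3).

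**The concern.** The question is directional, and its plainest reading includes how strongly the calf contracts. The scaling rule makes every cycle peak at 100% in every condition, so information on strength is gone before any comparison is made. The 20% threshold refers to the same peak, and the similarity index measures agreement without direction, so neither brings it back.

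What is at stake is the interpretation of a secondary outcome. If FES lowered calf activity evenly over the cycle, onset, duration and BDSI would all be unchanged, and that could be read as FES not reducing calf activation.

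**Working it through.** The plan gives no figure to reproduce here. The check is algebraic, followed by a simulation.

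**1. Algebra.** Let e(t) be the envelope of one cycle and g > 0 a uniform change in amplitude. Filtering, rectification and root mean square all scale with g, so the new envelope is g·e(t). After own-peak scaling:

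g·e(t) / max(g·e) = e(t) / max(e).

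Example for a 50% fall: a point at 0.30 under a peak of 1.00 scales to 0.30/1.00 = 0.30. After the fall it is 0.15/0.50 = 0.30. The averaged curve, the 20% crossing points, onset, duration and BDSI are therefore independent of g.

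**2. Simulation of the described steps** (band-pass 10–500 Hz, envelope over 100 ms, own-peak scaling, mean of 125 cycles, 20% rule). Assumptions not in the protocol: 2000 Hz sampling, a 1 s cycle, one bell-shaped stance burst, and low background activity that scales with the burst.

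| True calf activity | Mean of scaled curve | Active time, % of cycle | On/off match with base | Unscaled peak |
|---|---|---|---|---|
| Base | 0.243 | 33.4 | – | 0.64 |
| 25% lower | 0.243 | 33.2 | 100% | 0.49 |
| 50% lower | 0.243 | 33.3 | 100% | 0.32 |
| 75% lower | 0.244 | 33.6 | 100% | 0.16 |
| Shorter burst | 0.188 | 23.6 | 90% | 0.59 |
| Longer burst | 0.314 | 45.3 | 88% | 0.67 |

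The small differences in rows 1 to 4 are random variation between runs. The unscaled envelopes do recover the falls: 0.49/0.64 = 0.77, 0.32/0.64 = 0.50, 0.16/0.64 = 0.25.

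**3. What stays visible.** Duration separates a shorter from a longer burst. The match index barely does (90% against 88%). A selective fall also shows. For illustration, with assumed values, if the stance peak is unchanged and swing activity drops from 30% to 15% of peak, it crosses the 20% line and is scored inactive.

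**4. A fixed reference per visit.** Let P1 and P3 be a muscle's mean peak in conditions 1 and 3 of one visit. The ratio P1/P3 keeps the effect of the aid while worn: if wearing it halves the peak, the ratio halves. Two limits follow. Condition 3 over its own reference is P3/P3 = 1 at every visit, so a change in condition 3 between visits cancels. A lasting change h that acts equally with and without the aid also cancels, since h·P1/(h·P3) = P1/P3.

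**5. Stimulation spikes, conditional.** If a spike-driven envelope peak were k times the muscle's own peak, maximal muscle activity would scale to 1/k, which is below 20% when k > 5. The protocol gives no k for any channel. Simulated spikes, assumed to fall at 62–100% of the cycle at 17–40 pulses/s with calf activity unchanged, raised apparent active time from 33.4% to 62.2–76.5% at sizes of 1–3 times the peak EMG standard deviation. At size 30, active time before 60% of the cycle fell from 33.3% to 2.9%. The error can go in either direction, but only if spikes reach the calf channels and stay there.

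**The case against.** The strongest reply is that the protocol treats activation as on or off, and that duration has a direction. A decrease read as less active time can be tested, and so can a selective swing-phase fall, which matters because stimulation is delivered in swing. This stands. A reader might infer that the EMG question cannot be answered at all; the text does not support that. Own-peak scaling is also a reasonable choice for timing.

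Three further inferences are tempting and not supported.

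- **Spikes are left in the gait recordings.** The statement "Figure 3 shows the FES stimulation in the EMG as big spikes" concerns one tibialis anterior sensor in the timing set-up, which the protocol says is not used for gait analysis. Nothing documents spikes in gastrocnemius or soleus. The filter is described as "band-pass filtered at 10 to 500 Hz using a 4th order Butterworth filter to remove low frequency motion artefacts and high frequency noise", and no step for stimulation artefact is listed, but a condensed article may leave one out.
- **The fatigue analysis has the same flaw.** It is introduced as a separate analysis and is not said to be scaled to the peak.
- **A null amplitude result would be reported.** No amplitude output is planned from the scaled curve. The risk is that unchanged timing is taken for unchanged activation.

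What the reply does not reach is level. The scaling rule, threshold, index and question are all stated, and they do not fit together on that part. This is not a detail left to a fuller document.

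**Conclusion.** The point holds in limited form. As described, the EMG outputs can show changes in timing, duration or relative pattern of calf activity. They cannot show a uniform decrease in its level, and a uniform fall of any size gives zero expected change in onset, duration and BDSI. This follows from the scaling rule itself; the simulation only illustrates it, and its waveform is assumed. In real recordings, background noise that does not fall with the muscle signal would make the invariance approximate.

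The spike problem is conditional on calf-channel contamination that the protocol does not document. EMG is a secondary measure and is not among the parameters listed for the mixed models under Secondary outcomes. The primary Goal Attainment Scale analysis is unaffected.

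**What to change.** 1. Keep the own-peak curve for onset, duration and BDSI.
2. For gastrocnemius medialis and soleus, add an amplitude outcome scaled to one fixed reference per muscle per visit, for example the mean peak over the condition 3 cycles. Compare aid-on with aid-off within the visit, then compare that contrast between the FES and conventional phases.
3. Do not use this reference to compare condition 3 itself between visits, where it cancels the change. Limit without-aid comparisons across visits to timing and duration.
4. If no amplitude outcome is added, restate the question as burst timing and duration only.
5. If stimulation spikes appear in the calf channels of FES-on recordings, remove them before peaks and thresholds are computed, or drop those channels.

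The cost is a little extra processing and wording, and possibly the loss of some FES-on channels. Conditions 1 and 3 are already part of the gait analysis, so no new recordings are needed.

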#### Physical examination parameters (domain C)

A permanent team of a pediatric physiotherapist and a medical doctor performs the physical examination during the assessments. The physical examination consists of the following measurements:Passive - and active ranges of motion of the joints of the lower limb are measured with a goniometer, and angle of muscle reaction (no resistance, resistance, catch, clonus or immobile joint) according to the Modified Tardieu Scale for spasticity [49, 50].Selective control assessment of the lower extremity: the patient is asked to perform the following movements, one by one, left and right separately, without moving any other part of the body: hip flexion (in supine position), knee extension (sitting), ankle dorsiflexion (both supine and sitting) and eversion (sitting) of the foot. The score ranges from 0 (unable) to 2 (normal), score 1 means ‘impaired’ [51, 52].At the first appointment, anthropometric and static characteristics are collected, including body length and leg length (in centimeters), weight (in kilograms), valgus/varus deformity of knee and foot (more or less than 5°), and shape of scoliosis if present.

Appendix D shows the form used for the physical examination at the first appointment.

These characteristics are potential factors that may influence the efficacy of FES treatment and therefore, they will be registered and the relation with the final main results will be analyzed. Another relevant question on this level is: *Does FES decrease spasticity of the calf muscles?*

#### Strength of plantar- and dorsiflexors (domain C)

Hand-held dynamometry with the MicroFET2 device (Hoggan scientific, Salt Lake City, USA)) is used to measure the strength of the ankle plantarflexor muscles, both with straight knee (gastrocnemius muscle) and with knee flexed in 90° (soleus muscle), and the ankle dorsiflexor muscles [53, 54]. The lever arm between the lateral malleolus and the middle of the height of the MicroFET2 is measured in meters at the lateral side of the foot. The patient is stabilized and asked to gradually build up the force (‘make method’). The mean force value in Newton of three measurements is used to calculate the moment in Newtonmeter. At least 30 s of rest between measurements of the same muscle is provided. If the values differ more than 20%, a fourth measurement is performed to replace the devious value. For hand-held dynamometry in young children with cerebral palsy, smallest detectable differences of 9–30% are reported when using average values over at least two test occasions and 2–3 repetitions per muscle [54].

The relevant question on this level is: *Does FES change the force of the dorsiflexor and plantarflexor muscles of the foot, measured by hand-held dynamometry?*

#### Patient satisfaction

The satisfaction of patients with their walking aid will be measured using a visual analogue scale (VAS) with 6 smileys ranging from ‘worst’ to ‘best’.

Besides this VAS scale, the feelings about donning and doffing including footwear, measured in each phase of the study (AFO versus FES), will be taken in to account. We will use the question ‘How do you feel about your ability to dress yourself?’ from the CPQoL (as explained above) for this purpose and we will explain to the participants that footwear is included in this question about dressing.

#### Cost-utility and cost-effectiveness

The EuroQol Five Dimensions Health Questionnaire Youth (EQ-5D-Y) is a child friendly and reliable instrument to measure health related quality of life [55]. Percentages of agreement in test–retest reliability range between 69.8 and 99.7% [56]. It consists of six multiple choice questions (answers: no problems/some problems/a lot of problems with…) and a scale from 0 to 100 to grade the (subjective) health of the current day. The EQ-5D-Y will be used to calculate quality adjusted life years (QALYs) to analyze cost-utility. For the cost-effectiveness analysis, the additional costs of FES therapy are compared with the additional health effects, measured by the GAS (the primary outcome measure).

#### Characteristics for patient selection

The influence of the following aforementioned parameters on the primary outcome measure will be analyzed, as these could be relevant characteristics for selection of eligible patients: age, physical characteristics (ankle range of motion in sagittal plane, foot clearance, amount of spasticity), a history of botulinum toxin injections or surgeries, physical activity in daily life (stepping time and steps taken) and 6MWT distance (in meters). Besides, the characteristics of the MRI lesion will be taken into account:

*MRI pattern brain (domain C) -* Clinically available MRI scans will be used and classified according to the scale by Fiori et al. [57]. Type of lesion will be classified according to the classification system by Himmelmann et al. [58] The research question regarding patient characteristics is: do patients for whom FES treatment is successful have certain characteristics?

## Premature termination

### Withdrawal of an individual subject

Subjects can end participation in the study at any time, with or without providing a reason. The investigator can also decide to withdraw a subject for medical reasons. Subjects withdrawn from the study will continue to get normal clinical care and follow-up. Drop-outs will be replaced if necessary, to have at least 22 patients completing the study.

### Study monitoring board

A monitoring plan will be made with the Clinical Trial Center Maastricht (CTCM) according to the local guidelines. Monitoring will include verification of informed consents, (serious) adverse events or reactions, delegation log and signature list and verification of data against source documents and medical records. This monitoring board will provide recommendations for changes to the study protocol if necessary.

## Statistics

For all analyses, we will use IBM SPSS statistics version 24 or higher.

### Descriptive statistics

Patient characteristics including gender, age, GMFCS level, affected side, MRI pattern and ankle range of motion, and data from the gait analysis (based on 250 steps) will be described. The mean and standard deviation or median and first and third quartile will be used, depending on the distribution. The distributions will be checked using histograms and Q-Q plots.

### Primary outcome

GAS scores will be dichotomized in to ‘goal achieved’ (scores 0 to + 2) and ‘goal not achieved’ (scores − 1 to − 3). The McNemar test (non-parametric) will be applied to test whether the proportions of goal achievement are significantly different between the FES and conventional phase. Raw GAS scores will also be provided. Beside an analysis including the patients who completed the study, an intention to treat analysis will be performed including the patients who discontinued the study as ‘goal not achieved’ (‘worst case analysis’). A *p*-value of 0.05 is considered to be statistically significant in this analysis.

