#### Sample size calculation

The primary outcome measure will be the GAS, a 6-point scale which will be dichotomized into ‘goal achieved’ and ‘goal not achieved’. The difference is assumed to be clinically relevant if the proportion of participants achieving the goals is 30% higher for one of the treatment phases (conventional or FES). To be able to detect such a clinically relevant difference with a power of 80%, using an alpha of 5%, we need to include at least 22 participants – based on the crossover design. Previous studies reported 0–14% dropout [20, 21]. Taking possible dropout of 14% of the participants into account, 25 participants will be included. If 10 patients completed the study, an interim-analysis will be performed to check the power for the primary outcome.

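### The intention-to-treat 'worst case' codes every drop-out as a failure whatever the treatment; in a paired McNemar comparison that is not a worst case, and p can stay fixed or move either way

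*Protocol article*

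**What the plan says.** The Primary outcome section of the protocol article splits the Goal Attainment Scale into achieved and not achieved and names one test: "The McNemar test (non-parametric) will be applied to test whether the proportions of goal achievement are significantly different between the FES and conventional phase". It plans two analysis sets. The first is introduced with "Beside an analysis including the patients who completed the study". For the second, "an intention to treat analysis will be performed including the patients who discontinued the study as" not having achieved the goal, and the protocol calls this a worst case analysis. No other test is named for the second analysis. The section does not say whether the failure code covers both phases or only the missing one, nor whether an observed first-phase result is kept.

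Three other places bear on this. Under Sample size calculation, "we need to include at least 22 participants", raised to 25 for 14% drop-out. Under Withdrawal of an individual subject, "Drop-outs will be replaced if necessary, to have at least 22 patients completing the study". Under Randomization and blinding, both treatment orders are used, two and two in each block of four.

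**The concern.** A worst case for a treatment comparison has to depend on treatment: each missing result is filled in against the treatment whose benefit is being tested. Failure for everyone is a familiar conservative rule for a single success proportion, but it does not carry over to a within-patient comparison in which both members of the pair can receive the same code.

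This matters because the other primary analysis is restricted to completers, so this is the article's only stated guard against informative drop-out on the primary outcome. A report could say that the worst case analysis confirms the completer result when, under one reading of the rule, its p-value could not have differed. Under the other reading, the analysis could be more favourable to FES than the completer analysis it is meant to stress.

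**Working it through.** **Inputs.** From the protocol article: McNemar's test, significance level 0.05, 22 completers, 14% drop-out, 25 enrolled, both orders randomised. Assumed: two-sided testing (sidedness is not stated) and the discordant counts, since the protocol gives none.

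**The plan's own figure.** 22 × 1.14 = 25.08, which gives the stated 25. The expected number of drop-outs is therefore 25 − 22 = 3 (14% of 25 is 3.5).

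**Formula.** Let b be the pairs that favour FES and c those that favour conventional treatment. The exact two-sided p is 2 × P(X ≤ min(b, c)), with X binomial(b + c, 0.5). Concordant pairs do not enter. The risk difference is (b − c)/n, and there they do enter, through n.

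**What each kind of drop-out contributes.** A win is a pair for FES, a loss is a pair against it, and 0 is a concordant pair.

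| Drop-out | Both phases coded failure | Only missing phase coded failure | Bound against FES | Mirror image |
|---|---|---|---|---|
| Nothing observed, either order | 0 | 0 | loss | win |
| FES first, achieved, then left | 0 | win | 0 | win |
| FES first, not achieved, then left | 0 | 0 | loss | 0 |
| Conventional first, achieved, then left | 0 | loss | loss | 0 |
| Conventional first, not achieved, then left | 0 | 0 | 0 | win |

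The bound sets a missing FES phase to not achieved and a missing conventional phase to achieved; the mirror image reverses both. Coding only the missing phase agrees with the bound for conventional-first patients with an observed phase, agrees with the mirror image for FES-first patients with an observed phase, and agrees with neither when nothing was observed.

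**Both phases coded.** Start from 22 completers with 7 v 1: p = 2 × (1 + 8)/256 = 0.070. Add 3 drop-outs: still 7 v 1, p = 0.070. The risk difference goes from 6/22 = 27.3% to 6/25 = 24.0%.

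**Only the missing phase coded.**

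- One FES-first achiever who leaves: 7 v 1 becomes 8 v 1, p = 2 × (1 + 9)/512 = 0.039. A non-significant result becomes significant.
- One conventional-first achiever who leaves: 8 v 1 (p = 0.039) becomes 8 v 2, p = 2 × (1 + 10 + 45)/1024 = 0.109. Significance is lost.
- Three of the first kind from 7 v 1: 10 v 1, p = 2 × (1 + 11)/2048 = 0.012.
- Three of the second kind from 7 v 1: 7 v 4, p = 2 × (1 + 11 + 55 + 165 + 330)/2048 = 0.549.

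**Bound against FES.** Three drop-outs with nothing observed, from 7 v 1: 7 v 4, p = 0.549. The planned rule gives 0.070 for the same three patients under either reading.

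**The case against.** The strongest reply is that the rule has no built-in lean towards FES. A reader might infer from the FES-first example that the analysis either does nothing or helps FES. The documents do not support that: both orders are randomised, and a conventional-first achiever who leaves counts against FES. Three such patients give 7 v 4 under the planned rule, the same table as the bound gives for three patients without data. Direction of bias is not shown either. The protocol anticipates discomfort and intolerance of stimulation as side effects, so drop-out might cluster in the FES phase, but it gives no split. If it did cluster there, FES-first leavers would be concordant and conventional-first leavers neutral or against FES. All of this stands.

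It is also true that coding both phases is not wholly inert, since the risk difference shrinks. A reader might further infer that replaced drop-outs leave the analysis. Nothing says so: replacement is only as needed, and the intention-to-treat set expressly includes patients who discontinued.

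Two replies stand only in part. An article may leave to the full protocol or analysis plan which phase is coded. But the code and the label are both stated here, and neither reading makes the label true. And the sample size section treats a difference in favour of either phase as relevant, so worst need not mean worst for FES. A code that ignores treatment, however, is not a worst case for conventional treatment either. That argues for reporting both bounds.

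**Conclusion.** The point holds in this form: a uniform failure code is not a worst case under McNemar's test. With both phases coded, the test repeats the completer p-value exactly, whatever the number of drop-outs and whatever the discordant counts. With only the missing phase coded, p can fall or rise depending on treatment order and time of leaving, and in the illustrations a single drop-out crosses 0.05 in each direction.

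The p-values rest on assumed discordant counts and on exact two-sided testing; the table of contributions does not. The rule concerns about 3 of 25 patients in an analysis that accompanies the completer analysis. It is a flaw in a stated rule and worth correcting before analysis, but it does not show that the trial's result would be biased towards FES.

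**What to change.** In the Primary outcome section:

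- Keep every observed phase result for all randomised patients, and say that this includes drop-outs who are replaced under the withdrawal section.
- Replace the uniform code with a bound in which a missing FES phase is not achieved and a missing conventional phase is achieved, and keep the worst case label for that bound.
- Report the mirror image beside it, so that the reader sees the range that the missing data allow.
- Give the risk difference with each McNemar result.

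A logistic mixed model or generalised estimating equations on all observed phases is an optional addition. With about 25 patients and two binary results each, it is a matter of preference and not needed to correct the rule.

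The cost is one paragraph of wording and a few lines of code. The downside is that the bound is extreme, above all for patients with no phase observed, and will look less favourable than the present rule.
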